### Statistical analysis

All statistical analyses will be performed using the PASW software package (version 19, SPSS, Chicago, USA). Descriptive statistics will be used to describe the main characteristics of both research groups. Differences in rotational, coronal and sagittal alignment between the groups will be determined by using the nonparametric Mann-Whitney U-test for independent samples. For the clinical parameters, t-tests will be used for continuous values or the Mann-Whitney U-test when the variables are not normally distributed. A Chi-square test and a Fisher’s Exact test will be used for dichotomous values. For all test procedures, a p-value of < .05 will be considered to indicate statistical significance.

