### Radiographic evaluation

Rotational prosthetic alignment will be measured on a CT-scan of the operated leg. For evaluation of alignment in the coronal and sagittal planes a new imaging device, called the EOS system (Biospace Imaging, Paris, France) [28], will be used. This device is characterized by a reduction in radiation (800-1000 times less than for CT-scan and 10 times less than conventional X-ray) [28,29]. Reason for this is the use of an innovative technology called fast gaseous particle detectors, invented by George Charpak (which earned him the Nobel prize in physics in 1992). The EOS imaging device uses two orthogonal sources of radiation and linear detectors that are coupled together. These sources move up and down along the patient, producing an anterior-posterior and lateral image at the same time while the patient is in weightbearing position. This is a different technique than conventional radiograph systems, where beams are divergent in horizontal and vertical plane.

Of the patients in the intervention group, a CT-scan of the operated leg will be made postoperatively during the visits at the outpatient clinic. Patients included in the historical control group have already undergone the standard surgical technique for rTKA. A CT-scan of the operated leg will be made the next time the patient visits the outpatient clinic of the Orthopedic Department for follow-up of the rTKA.

For evaluation of rotational prosthetic alignment, rotation of the femoral and tibial components will be determined separately according to the Berger CT protocol [30]. Angles measured for rotational alignment are:

– Condylar twist angle for rotation of the femoral component: angle between the epicondylar axis and the prosthetic posterior condylar axis (inner border of posterior cut). Endorotation of the femoral component will be shown as a positive (+) angle and exorotation of the femoral component will be shown as a negative (-) angle. An angle of >3° endorotation or exorotation will be considered an outlier.

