### Sample size

The hypothesis is that the use of CAS leads to fewer outliers in prosthetic alignment compared to the use of mechanical alignment guides during rTKA. Primary outcome measure will be rotational prosthetic alignment. When using the conventional operation technique, around 25% of the knees is considered a radiological outlier. Therefore, a P2 value of 0.75 was chosen [21,36]. Previous research has shown that the use of CAS in TKA decreases the number of outliers by 17-30% [21,37,38]. When a 20% decrease in outliers is expected in the CAS group compared to the control group with P1 = 0.95, P2 = 0.75, power = 80% and alpha = 0.05, 44 patients per group are needed.

Since 2008 a total of amount of 21-30 rTKAs have been performed each year at UMCG, and an increase is expected. As a result of that, the possibility is expected of including 44 patients in the intervention group between September 2012 and September 2015. Inclusion of 44 patients in the historical control group is not expected to be a problem, as 165 rTKAs were performed between January 2002 and April 2012.

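### The trial is sized on the proportion of alignment outliers, but alignment is assigned a Mann-Whitney test, which on signed angles detects a shift and not closeness to target; no test is tied to the powered endpoint

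*Protocol article*

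**What the plan says.** All references are to the protocol article.

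- **Sample size, hypothesis:** "The hypothesis is that the use of CAS leads to fewer outliers in prosthetic alignment compared to the use of mechanical alignment guides during rTKA".
- **Sample size, outcome:** "Primary outcome measure will be rotational prosthetic alignment". Whether this means the angle or the outlier flag is not stated.
- **Sample size, planning figures:** with the conventional technique, "around 25% of the knees is considered a radiological outlier"; the calculation reads "P1 = 0.95, P2 = 0.75, power = 80% and alpha = 0.05, 44 patients per group are needed".
- **Radiographic evaluation:** femoral and tibial rotation are measured separately, and each is recorded with a sign. For the femur: "Endorotation of the femoral component will be shown as a positive (+) angle and exorotation of the femoral component will be shown as a negative (-) angle". The tibia follows the same convention, with 18° endorotation taken as normal. An outlier lies more than 3° away in either direction.
- **Statistical analysis:** "Differences in rotational, coronal and sagittal alignment between the groups will be determined by using the nonparametric Mann-Whitney U-test for independent samples". The next sentence gives t-tests or Mann-Whitney for the clinical parameters. A further sentence gives chi-square and Fisher's exact tests for dichotomous variables, without mentioning outliers. Every test uses p < .05. Absolute deviation from target is not mentioned anywhere.

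**The concern.** The hypothesis is about accuracy: fewer knees far from target on either side. The outcome named as primary, rotational alignment, is assigned by that same name to a test of location. If the recorded signed angles enter that test, an error of +5° and an error of -5° sit at opposite ends of the ranking and offset each other. A group tightly clustered on target and a group widely scattered around it then have similar rank sums.

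Two things are at stake. First, the 80% power was computed for a comparison of proportions and does not carry over to this test. Second, a significant result would show that the angles differ between groups, not which group is nearer the target.

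**Working it through.** **1. The plan's own figure.** Inputs from Sample size: outlier-free proportions 0.95 and 0.75, power 80%, alpha 0.05 (taken as two-sided; the text does not say).

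Arcsine formula: h = 2·asin(√0.95) − 2·asin(√0.75) = 0.596.
n = 2(1.960 + 0.842)² / h² = 44.2 per group.

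This matches the stated 44 (power at 44 is 79.9%). The sample size is therefore for two proportions, not for a rank test on angles.

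**2. Spread implied by the planned rates.** The protocol gives no mean or SD for any angle, so these are assumptions. For normal errors centred on target, P(|deviation| > 3°) fixes the SD:

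- Control, 25% outliers: SD = 3 / 1.150 = 2.61°.
- CAS, 5% outliers: SD = 3 / 1.960 = 1.53°.

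**3. Mann-Whitney on signed angles.** If both groups are symmetric about the same centre, P(control angle > CAS angle) = 0.5 whatever the two SDs are. The test then rejects at roughly its alpha level. Simulation (40,000 trials, 44 vs 44, two-sided 0.05, one angle per patient, SDs re-solved in the shifted cases so that the rates stay at 25% and 5%):

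| Scenario | Power, signed angles | Power, absolute deviation |
|---|---|---|
| Both on target, normal | 5.3% | 75.5% |
| Both on target, t with 4 df | 5.6% | 89.5% |
| Both on target, Laplace | 5.2% | 86.1% |
| Both on target, uniform | 5.0% | 40.0% |
| Both off by 0.5° | 5.4% | 75.6% |
| Both off by 1° | 5.9% | 66.9% |
| Control off by 0.5°, CAS on target | 19.4% | 76.3% |
| Control off by 1°, CAS on target | 60.6% | 76.1% |
| Control off by 1.5°, CAS on target | 96.0% | 78.8% |

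Power on signed angles thus depends almost entirely on a difference in centre, which the sample size section does not mention.

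**4. What a significant result would mean.** Take two equally accurate groups with mirrored bias, means +0.75° and −0.75°, SD 2° (illustrative assumptions). Each has P(|deviation| > 3°) = P(Z > 1.125) + P(Z < −1.875) = 0.130 + 0.030 = 16% outliers. The signed Mann-Whitney test rejects in about 92% of trials; on absolute deviation it rejects in about 5%. Significance on signed angles is not evidence of better alignment.

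**5. Testing the outlier proportion directly.** Exact power at 25% vs 5%, 44 per group:

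- Pearson chi-square, uncorrected: 80.4%
- Fisher's exact: 69.5%
- Chi-square with Yates correction: 66.4%

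Only the first delivers the planned 80%.

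**The case against.** Four counter-arguments deserve weight.

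- **The scale is not stated.** The Statistical analysis section does not say that signed values enter the test, and the sign rule describes how rotation is recorded. It is given for the two rotational angles only, not for the coronal and sagittal ones. This stands as a limit: signed values are an inference. It is a fair one for rotation, because no other rotational value is defined.
- **Suitable tests are listed.** The sentence on chi-square and Fisher's tests is not restricted to clinical parameters, and the outlier flags are among the few variables that the protocol itself dichotomises. This stands in part. The sentence could cover outliers, but then the primary outcome has two kinds of test, each at .05, with no statement of which decides, and the choice moves power between 80% and about 66%.
- **The 5% figure is conditional.** It needs a common centre. The Historical control group section says that positioning used the same landmarks in both groups, which makes a common centre plausible but does not establish it. The Background says landmarks are often lost in revision; nothing says whether the resulting errors are symmetric. The range has to be shown.
- **This is a condensed article.** Detail may sit in a fuller document. That would excuse silence, but here the article states a test for the outcome it calls primary, and that test does not match the stated hypothesis.

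A reader might infer that the trial would miss its planned effect about 95% of the time, or that it cannot answer its question at all. The documents support neither. The 95% miss rate applies only to signed angles with a common centre, and a listed test applied to outlier yes/no could answer the question.

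**Conclusion.** The mismatch is real: the hypothesis and sample size concern a two-sided outlier proportion, while the test assigned to alignment is one of location. Read with the signed angles that the protocol defines, that test has about 5% power at the planned 25% vs 5% if the groups differ only in spread. Power rises to about 19%, 61% or 96% if controls are biased by 0.5°, 1° or 1.5° and CAS is on target. Even a significant result would leave open which group is nearer the target.

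These figures assume one angle per patient, 44 per group, two-sided 0.05 and, except where another shape is named, normal errors. What needs correcting is that no test is tied to the powered endpoint and none is named as decisive. It should be settled before analysis, because it determines what the primary result means.

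**What to change.** In Statistical analysis:

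1. Name the proportion of rotational outliers as the primary comparison. State whether femoral, tibial or either component counts, and that deviation is measured from each component's stated target (for the tibia, the 18° that the protocol calls normal).
2. Test it by uncorrected Pearson chi-square, with the risk difference and 95% CI. If Fisher's test is preferred, restate the power (about 70% at 44 per group).
3. Make Mann-Whitney on absolute deviation from target the supportive continuous analysis. Its power is about 76% in the centred normal case and 40% to 90% over the other centred shapes. For the coronal and sagittal angles, state the reference value for each; only the sagittal tibial slope has one (7°).
4. Report signed angles descriptively, to show the direction of any bias.

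Cost: analysis wording only. No new data or measurements are needed, and the sample size stands if uncorrected chi-square is the named test.

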## Discussion

Correct prosthetic alignment is important for a good clinical outcome after TKA. More accurate alignment after TKA correlates with less pain, better knee function, faster rehabilitation and improved quality of life [39,40]. Rotational malalignment has a negative effect on patellar tracking, stability, pain and overall biomechanics of the knee joint [30,41-44], while malalignment in the coronal and sagittal planes leads to an increased risk of loosening, pain and instability [31,34,45,46]. Accurate prosthetic alignment is therefore essential during primary and revision TKA, to postpone revision and rerevision procedures.

In recent years, CAS has become a frequently used technique for improving prosthetic alignment in primary TKA, and several studies have shown its benefits. CAS significantly improves varus/valgus angle [15,17-20,47], mLDFA [16,17,21-23], mMPTA [16,17,20,21,23], femoral flexion angle [15,16,18,21,22], tibial downslope [15,18,20,22,23] and rotational alignment for the femoral and tibial components [15,16,20]. Perlick et al. [25] revealed a significantly better mechanical limb axis and coronal alignment of the femoral component when CAS was used during rTKA. Correct alignment of the prosthesis is even more difficult during rTKA compared to primary TKA because of extensive bone loss and the disappearance of anatomical landmarks. This may imply the expectation of an even greater advantage of CAS in rTKA compared to primary TKA. However, literature about the use of CAS in rTKA is scarce [25,26,48,49]. Moreover, patient groups in these studies are small and only one study has compared postoperative prosthetic alignment with a control group. Furthermore, potential differences in rotational alignment of the prosthesis have not yet been investigated.

In conclusion, it is our expectation that this study will provide insight into the effectiveness of CAS in rTKA on postoperative prosthetic alignment. It is our hypothesis that the use of CAS in rTKA leads to improved prosthetic alignment compared to conventional rTKA.
